#### Recruitment and selection of the participants

Regularly, employees were registered on their first day of sick leave by the OHS (figure 1). Since January 2002, each employee on sick leave due to mental health problems was invited to meet with a case manager of the OHS within one week. This case manager informed the employee about the study and planned a consultation with an OP in the first two weeks of sick leave. To enhance recruitment one of the researchers (DB), who was allowed to check the registration system of the OHSs, informed the OP when a potential participant would come for consultation. Each employee who consulted an OP, and was still on sick leave due to mental health problems, was then asked by the OP to participate in the study. After an employee had signed informed consent during this consultation (T0), the OP unsealed a study envelope containing the allocated treatment for the patient, and sent the signed informed consent to the researcher (DR). In the same consultation the employee received the baseline questionnaires and was asked to return this questionnaire to the researcher after completion.

**Figure 1 F1:**
[figure not shown]
Flow chart of time line, study design and return to work.

#### In- and exclusion criteria

As the guideline focuses on all kinds of mental health problems, we aimed to include employees with a broad range of mental health problems consulting their OP. Employees were included if they met the following inclusion criteria:

• Mental health problems according to the diagnosis of the OP

• Sick leave at the moment of inclusion

• Sick leave period did not start before 2002.

Exclusion criteria were the same as stated in the OP-guideline:

• Mental health symptoms that were caused by somatic illness

• Disagreement between OP and employee about the diagnosis

• Lack of confidence in the relation between OP and employee

The application of the exclusion criteria was dependent on the OPs expert judgement. To prevent selection bias, employees were not included of whom the period of sick leave started before 2002.

### Randomisation

Block randomisation (size 50) was done on the patient level before the start of the study using SPSS. The randomisation results were sealed in 250 consecutive envelopes. The OPs were informed about the study procedure and received sealed numbered envelopes, in which the treatment was stated which they had to provide. They were allowed to open an envelope only after an employee voluntarily signed an informed consent. Then the OP told the participant to which treatment her or she was assigned.

To minimize the risk of irregularities by letting OPs open their treatment concealment themselves, randomisation was checked by an independent researcher ([name]) one year after the start of the study. At the end of the study this procedure was repeated by checking the treatment allocation of all the in- and excluded persons.

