### Study population: sample size and power analysis

In order to detect a relevant difference in survival analysis on our primary outcome return to work, nQuery Advisor [37] was used to calculate the sample size. Proportions used to determine the sample size needed, were analysed from sick leave data of the police constabularies in 1999. In 1999, 286 employees were registered as being on sick leave due to mental health problems, which was 6.6 % of the total sick leave registrations. Their duration of sick leave in 1999 was 35.5 % of the total volume of sick leave, with an average of three months per case. With a power of 90%, at a 0.05 level, a two-sided log-rank test for equality of survival curves was done, assuming a difference between the intervention and control group proportion still on sick leave after one year of 0.25. This test indicated that a sample size was needed of 107 in each group. Assuming a dropout rate of 20%, inclusion of a total of 268 patients was necessary to statistically detect a clinically relevant difference.

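### The allocation list as described holds 250 places, 18 fewer than the 268 patients the sample size section calls necessary, and the two figures need reconciling

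*Protocol article*

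**What the plan says.** The Randomisation section describes a list generated in advance: "Block randomisation (size 50) was done on the patient level before the start of the study using SPSS". It continues: "The randomisation results were sealed in 250 consecutive envelopes". One envelope is used per consenting employee: "They were allowed to open an envelope only after an employee voluntarily signed an informed consent".

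The section on sample size and power gives the basis of the calculation: "With a power of 90%, at a 0.05 level, a two-sided log-rank test for equality of survival curves was done". The effect to be detected is expressed as a contrast between the arms at the end of follow-up: "assuming a difference between the intervention and control group proportion still on sick leave after one year of 0.25". It then reports the result: "This test indicated that a sample size was needed of 107 in each group". The final step is: "Assuming a dropout rate of 20%, inclusion of a total of 268 patients was necessary to statistically detect a clinically relevant difference".

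The two proportions behind the difference of 0.25 are not given; the section says only that the proportions used came from 1999 police sick leave data. The article does not mention a further block, an extended list, or a reason for preparing 250 envelopes. The Study design section says that recruitment ended in January 2005.

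**The concern.** Both numbers are printed as facts about the same trial, and they conflict. If each randomised patient uses one envelope and 250 were made, 250 is the most the described list can allocate, yet the article calls 268 necessary. Block rounding does not explain it: 250 is exactly five blocks of 50, while reaching 268 would take a sixth block, or 300 envelopes.

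A reader who relies on the article for the planned size and power cannot tell which figure governed the trial. Either the list fell short of a correct target, or the target is overstated, or the envelope count is incomplete. Each possibility implies a different correction.

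**Working it through.** **Inputs.** From the Randomisation section: 250 envelopes, block size 50. From the sample size section: 90% power, two-sided 0.05, log-rank test, difference of 0.25 in the proportion still on sick leave at one year, 107 per group, 20% dropout, 268 in total.

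**1. Reproduce the 268.** 2 × 107 = 214; 214 / 0.8 = 267.5, rounded up to 268. The stated total follows from 107 per group and 20% dropout.

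**2. Compare with the list.** 268 − 250 = 18, and 18 / 268 = 6.7%.

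**3. Power if 107 per group is taken as giving 90%.**
- Patients left at 20% loss: 250 × 0.8 = 200, or 100 per group.
- Scaling: power = Φ[(1.960 + 1.282) × √(n/107) − 1.960].
- At n = 100: Φ[3.2415 × √(100/107) − 1.960] = Φ(1.174) = 88.0%.
- Loss at which 107 per group is just kept: 1 − 214/250 = 14.4%.
- With no loss (125 per group) the same formula gives 93.9%.

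**4. Does 107 follow from the stated difference?** The base proportions are not given, so all pairs p1 − p2 = 0.25 were scanned. With h = ln(p1)/ln(p2), Freedman's formula is

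n per group = (1.960 + 1.282)² × [(1 + h)/(1 − h)]² / (2 − p1 − p2).

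Its maximum is at p1 = 0.658, p2 = 0.408. There h = 0.467, and n = 10.507 × (1.467/0.533)² / 0.934 = 85.2, so 86 per group. Other formulas give these maxima at 90% power:

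| Method | Largest n per group for a 0.25 difference |
|---|---|
| Freedman log-rank | 86 |
| Schoenfeld log-rank | 78 |
| Two proportions | 82 |
| Two proportions, continuity correction | 90 |

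None reaches 107. By Freedman's formula, 107 per group at 90% power corresponds to a difference of about 0.22 (maximum 108.7 per group at 0.22), not 0.25.

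**5. Power at 100 per group computed from the 0.25 difference.** With Freedman's approximation at the least favourable pair, the expected events are 100 × 0.934 = 93.4, and power = Φ[√93.4 × (0.533/1.467) − 1.960] = Φ(1.55) = 94.0%. The minimum over all base proportions is 95.7% by Schoenfeld and 94.8% by two proportions.

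Steps 4 and 5 assume full one-year follow-up of the patients counted; the log-rank formulas also assume proportional hazards.

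**The case against.** The strongest objection is that 268, not 250, may be the faulty figure. The 0.25 difference needs at most 85.2 per group by Freedman's formula, and 85.2 / 0.8 = 106.5, which rounds up to 107. So 107 may already include the 20% dropout, in which case 268 counts dropout twice and 250 is ample. The article does not confirm this, but the possibility stands. It is why 268 cannot be treated as a sound benchmark and why the 107 has to be re-derived first.

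A second objection is that the envelopes prepared at the start need not be a cap. A block could have been added, and a journal article condenses the full protocol. That is fair as far as it goes, and the article does not report the number actually randomised. It does not remove the conflict in print, because if a block was added the Randomisation section is incomplete and should say so.

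A third objection is that 20% loss may be too pessimistic for the primary outcome. Table 1 takes return to work from the company database, and the text treats the employer's record as the reference standard, so loss need not follow questionnaire dropout. In a log-rank analysis, patients lost part-way also contribute time up to censoring. This stands, and it makes any effect on power smaller still.

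A reader might infer that the trial is underpowered, because 250 envelopes cannot deliver 90% power. The documents do not support that. The inference depends wholly on accepting 107 per group as exactly 90%, and the stated difference contradicts that 107.

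**Conclusion.** The mismatch in size is certain and rests on no power formula: the list as described allocates at most 250, which is 18 (6.7%) below the 268 stated as necessary, and the article does not reconcile the two.

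A loss of power is not established. It appears only if 107 per group is taken as giving 90%. Even then, at the plan's own 20% loss, it is about 2 points (90% to 88.0%), and it disappears if loss is at most 14.4%. On the stated difference of 0.25, 100 per group still gives at least about 94%, assuming proportional hazards and full one-year follow-up, whatever the base proportions. The two routes disagree because 107 and 0.25 do not fit together. The sample size statement therefore needs correction in its own right, and no single power figure for 250 can be given until that is done.

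**What to change.** Do not enrol more patients; recruitment has closed. In the article:

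1. State in the Randomisation section that 250 was the maximum number that could be randomised or, if the list was extended, correct the envelope count and say when and by how much.
2. Give the two base proportions behind the 0.25 difference, as taken from the 1999 sick leave data and not from trial results, with the formula or software option used. Re-derive the number per group from them, and say whether it already includes dropout.
3. Correct the 268 accordingly.
4. Restate the power for 250 from those inputs, with a loss assumption suited to the register-based primary outcome. Neither 88% nor 94% should be entered as a flat figure beforehand: the first inherits the unverified 107, and the second is a lower bound over unknown base proportions.

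The cost is one short recalculation and a few corrected sentences. Neither the design nor the analysis changes.

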### Blinding

Participants, employers and OPs were not blinded for the intervention. The researchers were blinded and did not know the treatment allocation of the employee, to prevent any influence on the study procedure. As this is an effectiveness study researchers were blinded for protocol compliance as well, to make the trial as realistic as possible. Blinding of the gathered sick leave and medical files data was secured, since these measurements were gathered from the automated databases of the police constabularies, the insurance agency and the OHSs.

### Interventions

#### Usual care

In this study the aim was to compare usual care of employees with mental health problems with an intervention. Usual care consisted of minimal involvement of the OP and access to treatment by a psychologist, as this represents daily practice. As the aim was to deliver the best optional care to our study population, optimal usual care was provided in this study. This consisted of the advice to OPs to refer to a psychologist, whose treatment was fully funded by the DGVP. The OP could refer to a psychologist working for a commercial multidisciplinary rehabilitation center, i.e. De Gezonde Zaak (DGZ), as this was part of an agreement with the OHS Commit. A patient was only referred if according to the expert judgement of the OP this made sense to the health condition of this person.

DGZ is one of the largest Dutch commercial psychotherapeutic intervention centers, which focuses on return to work of the employee. DGZ is located in different parts of the country. Besides physical therapists, around 100 psychologists are working for this organization. The psychologists are working according to cognitive behavioral principals. The standard therapy offered was based on protocols of the Dutch Institute for Work and Stress [20].

#### Intervention

The intervention consisted of treatment by OPs according to the guideline of employees on sick leave due to mental health problems. The guideline promotes a more active role of the OP as case and care manager facilitating return to work of the employee. The guideline is based on an activating approach, time contingent process evaluation and cognitive behavioral principles. The latter mainly concern stress inoculation training and graded activity and aim to enhance the problem-solving capacity of patients in relation to their work environment.

The guideline focuses on four aspects of the management of mental health problems. First, an early and activating guidance by the OP is promoted, in which return to work is part of the recovery process, even if the mental health problems are not related to work. Second, a simplified classification of mental health problems is introduced, with only four categories: 1) adjustment disorder (distress, nervous breakdown, burnout), 2) depression, 3) anxiety, and 4) other psychiatric disorders. Third, the OP acts as case manager, who is stimulated to be a care manager by counselling employees with adjustment disorders and work-related problems. Fourth, the OP performs a time contingent process evaluation and intervenes when recovery stagnates.

OPs participating in the study received training in the guideline before the study started. During this training, consisting of a three-day course with 10–15 other OPs, knowledge about and practice in working with the guideline were educated and exchanged [21]. The course reflected the guideline by training OPs in multiple cognitive-behavioral prescriptive interventions, to stimulate the patients' acquisition of problem solving skills, and to structure the patients' daily activities. Information was given and OPs were trained to differentiate between adjustment disorder and depression, anxiety and other psychiatric disorders. Questionnaires were introduced, which can be helpful in making an accurate diagnosis. In addition, a graded activity treatment approach was introduced, which was based on a three stages model. This treatment approach resembles stress inoculation training, a highly effective form of cognitive behavioral treatment [16]. In the first stage, there is emphasis on information: understanding the origin and cause of the loss of control. Patients are also stimulated to do more non-demanding daily activities. In the second stage, patients are asked to draw up an inventory of stressors and to develop problem solving strategies for the causes of stress. In the third stage, patients put these problem solving strategies into practice and extend their activities to include more demanding ones. The patients' own responsibility and active role in the recovery process was emphasized and the same goes for the importance of an early start of the intervention aimed at the acquisition of coping skills and at regaining control. Problem solving activities according to a time contingent scheme were educated and practiced. The OPs were free to choose the specific tools for use in each phase of the process. The training course was given by four persons: an experienced OP/psychologist, a psychologist/therapist, an experienced general practitioner/researcher on emotional distress, and a psychiatrist.

#### Co-interventions

Co-interventions cannot always be avoided. In case of post traumatic stress disorders, patients were also referred to a specialized trauma centre according to a special protocol of the DGVP. As the rehabilitation centre DGZ worked with multiple disciplines, it is possible that some patients in the control group received a combined intervention for mental and physical complaints by a psychologist and a physical therapist. In both the intervention and control groups co-interventions were registered in the medical files of the OHS and the database of the DGVP. These data can be used to adjust for co-interventions in the final multivariate analyses.

#### Compliance

As this is an effectiveness trial, we tried to mimic a realistic situation in both treatment groups. Therefore, no activities were undertaken to improve the actual treatment compliance by the OP with the allocated treatment. Treatment compliance of the OPs was examined by measuring guideline adherence and assessing the proportion of referrals by the OP in both groups to the psychologist of DGZ. Patient compliance of the treatment was examined by registering no shows of patients during consultations with the OP were, as this may give information about the willingness of the patient to adhere to the treatment.

#### Contamination

As randomization was done on patient level, OPs which were trained in the guideline treated all participants. Obviously this situation created a risk of treatment contamination between the groups. The trained OP treated an employee in the intervention group according to the guideline, as far as this happens in practice. The same OP treated an employee in the control group with minimal involvement and if applicable, direct referral to a psychologist. A cross-over learning effect may have happened in the control group, since the OP can adhere to the guideline in this group as well. The other way around, the OP may have referred an employee in the intervention group to a psychologist as well. The guideline promotes this in case of stagnation in recovery or in case of severe mental health problems of the employee. However, we tried to maximize the contrast by creating a situation in which referral to the psychologist in the control group was always granted by the insurance company (DGVP).

### Primary outcomes

#### Return to work

Return to work (RTW) was chosen as the primary outcome in this study [22]. A follow-up time of one year after inclusion was chosen, as effects of the intervention on return to work were expected to happen in this period. The RTW-outcomes are visualised in a time line in figure 2.

**Figure 2 F2:**
[figure not shown]
Timeline of measured sick leave data of a potential participant.

The primary outcome measure described in our study is full RTW: i.e. duration of sick leave due to mental health problems in calendar days from the first day of sick leave to full return to work in own or equal earnings (table 1). In addition, the net return to work to own or equal work was measured. This is the net duration of sick leave due to mental health problems in hours of full work absenteeism from the first day of sick leave to full return to work with own or equal earnings. The difference with full RTW is that the hours of partial return to work and % contract working hours (36 hours = 100%) are converted into the number of hours of full work absenteeism [23]. This may result in a more precise measure of RTW, when compared to full RTW. As figure 2 shows, net and full RTW consider the time period between T0 and T3, in which data collection by questionnaires took place (figure 1).

**Table 1 T1:** Measured data and their instruments and timing of data collection

**Data**	**Instrument**	**Base-line**	**Follow up**			
**Data related to primary outcomes**		**T0**	**T1**	**T2**	**T3**	**T4**
Return to work						
Full Return to work	Database company	X			X	
Net return to work	Database company	X			X	
First (partial or full) return to work	Database company	X	X	X	X	
Time until 1^st ^recurrence	Database company	X				X
Number and days of recurrences of sick leave	Database company				X	X
Total days of sick leave during one year follow up	Database company	X			X	X
Treatment satisfaction						
Treatment satisfaction of employee	Questionnaire		X	X	X	
Treatment satisfaction of employer	Questionnaire		X	X	X	
Treatment satisfaction of the OP	Questionnaire				X	

**Data related to secondary outcome**						

Cost effectiveness						
Direct costs of treatment						
• Consultations OP and treatment OHS	Medical files OHS	X	X	X	X	
• Consultations of participating psychologist centre	Medical files centre	X	X	X	X	
• Consultation of general practitioner	Insurance company	X	X	X	X	
• Consultations psychiatrist/psychologist/alternative therapist	Insurance company	X	X	X	X	
• Medication	Insurance company	X	X	X	X	
Indirect costs of lost productivity						
• Net lasting RTW and earnings	Database company	X			X	
• Replacement	Database company	X			X	

**Data related to prognostic measures**						

I) Personal characteristics						
Gender, Age	Database company	X				
Severity disorder: DASS/HADS (effect modifier)	Questionnaires		X			
Work-relatedness of the disorder	Medical files OHS	X				
Sick leave in year before inclusion (effect modifier)	Database company	X				
II) Treatment						
Treating occupational physician (OP)	Medical files OHS	X				
Diagnosis made by the OP	Medical files OHS	X				
Guideline adherence of the OP	Medical files OHS	X	X	X	X	
III) Work characteristics						
Type of function	Database company	X				
Number of working hours	Database company	X				
Police constabulary	Database company	X				

Another primary outcome variable that is part of the RTW process is first RTW: i.e. the duration of sick leave due to mental health problems in calendar days to first (partial or full) return to own or equal work. Other variables are related to recurrences of sick leave periods in the one year follow-up (T4)(table 1). These variables are the time in calendar days until the first recurrence of sick leave takes place and the number of and days during recurrences [21]. Total days of sick leave during follow-up is a primary outcome variables as well.

There was double registration of sick leave data, as both the employer and the OHS have their own registration system. The aim was to compare data of both systems, with the sick leave data of the employer as the 'golden standard'. This additional effort was done as reliable sick leave data are hard to get, since there is a known discrepancy with self-reported sick leave [24,25].

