## Methods/Design

### Study design

In a randomized controlled trial (RCT) the effect of the 'Dutch national guideline on the management of employees with mental health problems by OPs' was evaluated. The focus of this study is to examine the new, more active role of Dutch OPs according to the new guideline. Therefore, subjects in the intervention group were treated by OPs, who were trained to provide treatment according to the guideline. The control group received usual care, with minimal involvement of the OP and if applicable, access to treatment by a psychologist.

The first hypothesis of this study is that the intervention will lead to health gain for employees on sick leave due to common mental health problems. This will result in faster recovery, less stagnation and less referrals to psychologists. Counseling, instead of symptom based treatment, will result in earlier return to work and consequently a decrease of productivity loss. The second hypothesis is that the intervention will additionally lead to relatively more treatment satisfaction of the employee, the employer and the OP. The third hypothesis is that a decrease of productivity loss and prevention of expensive referrals to secondary care, will reduce costs.

The recruitment of participants for the study started in January 2002 and ended in January 2005. There was a one year follow-up. The study was funded by the Dutch Ministry of Internal Affairs and Kingdom Relations, and the Insurance Agency on Medical Guidance of the Dutch Police (DGVP). The study design, protocol and procedures were approved by the Medical Ethics Review Committee of the VU University Medical Centre.

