	*IF patient receives effective treatment in curative sector*	PI8 = NA

**PI9**	**Advice on return to work**	

	1. Advice on return to work should be provided by OP	
	2. IF no impediments for return to work are present, THEN OP should advise full or partial return to work	
	*One or both criteria not met at each consultation?*	PI9 = 1
	*Patient already (partially) returned to work?*	PI9 = NA

**PI10**	**Timing of consultations**	

	1. First consultation should be within 3 weeks from first day of sickness absence	
	2. IF patient has not yet completely recovered, THEN next consultation should be within 4 weeks from previous consultation	
	*Criterion 1 not met at first consultation OR criterion 2 not met at consultation 2 or 3?*	PI10 = 1

Additionally, this audit gave us information about treatment compliance by the OP (guideline adherence) in both groups. In this way contamination between the study groups was studied as well. Adherence in the intervention group was considered compliant if there was adequate adherence. Guideline adherence in the control group was considered compliant if there was deviant adherence.

The performance indicators will be assessed on their criteria by three independent researchers, resulting in a dichotomised score on guideline adherence for each employee (adequate versus deviant).

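### First (partial or full) return to work is a primary outcome variable, but entry does not require that this event is still to come, so it can precede randomisation

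*Protocol article*

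**What the plan says.** All references are to the protocol article.

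- **Status and event** (Primary outcomes, Return to work, text after Table 1): "Another primary outcome variable that is part of the RTW process is first RTW". It is defined as "the duration of sick leave due to mental health problems in calendar days to first (partial or full) return to own or equal work", so the event is the first return, partial or full. The sentence gives no starting point for the duration.
- **Clock for full RTW** (same section, text under Figure 2): "from the first day of sick leave to full return to work in own or equal earnings". The clock starts before T0. The T0 to T3 window given there covers net and full RTW only.
- **Entry** (In- and exclusion criteria): "Sick leave at the moment of inclusion" and "Sick leave period did not start before 2002". No exclusion concerns partial resumption.
- **Allocation** (Recruitment and selection of the participants): the occupational physician (OP) opens the envelope at the consultation in which consent is signed, T0. That consultation was planned for the first two weeks of sick leave.
- **Meaning of sick leave**: Evaluation of productivity loss says that police employees remain on sick leave until they can do all their tasks. Cost-effectiveness measures recognises partial sick leave. The definition of net RTW converts hours of partial return within the sick-leave period.
- **Analysis** (Data analysis): the recurrent-event Cox model counts only transitions to full RTW. It includes the sick-leave state up to inclusion as a covariate.

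**The concern.** A time-to-event outcome in a randomised comparison needs patients who are event-free at allocation. For full RTW the entry criterion secures this, because anyone fully back at work is no longer on sick leave. For first RTW it does not, because partial work is compatible with being on sick leave.

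A patient working some hours at T0 has a first-RTW time that was fixed before allocation. On average such times are the same in both arms. Kept in the analysis, they dilute the treatment difference and make patients who could no longer respond look like early responders. First RTW lies close to what the intervention aims at, namely early activating guidance and graded activity, so a diluted comparison here could hide a real effect.

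**Working it through.** **Step 1. Can the event precede allocation?**

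| Element | What the article fixes | Consequence |
|---|---|---|
| Event | "in calendar days to first (partial or full) return to own or equal work" | One partial resumption is enough |
| Entry | "Sick leave at the moment of inclusion" | Full absence is not required |
| Sick leave | Ends only at full duty | Part-time work at T0 is still sick leave |
| Allocation | Envelope opened at T0 | An earlier resumption is a pre-randomisation event |

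The four rows together show that it can. No rule in the article removes such events from first RTW or places the patient at risk only from T0. If the clock stated for full RTW carries over, pre-T0 events enter the outcome as short positive durations.

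**Step 2. Does the covariate in Data analysis deal with it?** No. It belongs to the model whose event is full RTW. An adjustment term also cannot turn an event that precedes allocation into one that follows it.

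**Step 3. How large could the effect be?** The article gives no share of patients partly at work at T0 (call it p) and no expected effect on first RTW. Everything in this step rests on assumptions and serves as illustration.

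*Mean difference.* Affected patients contribute zero difference on average, so observed difference = true difference × (1 − p). For an assumed 30 days:

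- p = 5%: 30 × 0.95 = 28.5
- p = 10%: 30 × 0.90 = 27
- p = 20%: 30 × 0.80 = 24
- p = 30%: 30 × 0.70 = 21

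*Hazard ratio.* Assume exponential times from T0 with means of 60 and 90 days, so the true hazard ratio is 90/60 = 1.5. Assume T0 on day 14, pre-T0 events spread over days 0 to 14 in both arms, and follow-up of 365 days after T0. Simulation with 20,000 patients per arm and 20 repeats, fitting a Cox model with the affected patients kept in, gives the third column below.

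*Power.* Suppose first RTW had 90% power at a two-sided 0.05 level before any patient is affected. These are the values the article uses for its return-to-work sample size. With 1.960 + 1.282 = 3.242:

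- affected patients kept, effect diluted: power = Φ(3.242 × (1 − p) − 1.960)
- affected patients left out: power = Φ(3.242 × √(1 − p) − 1.960)

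For p = 10% these are Φ(2.917 − 1.960) = Φ(0.957) = 83.1% and Φ(3.075 − 1.960) = Φ(1.115) = 86.8%.

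| p | Mean difference (days) | Estimated HR (true 1.5) | Power, kept | Power, left out |
|---|---|---|---|---|
| 5% | 28.5 | 1.47 | 86.9% | 88.5% |
| 10% | 27 | 1.44 | 83.1% | 86.8% |
| 20% | 24 | 1.38 | 73.7% | 82.6% |
| 30% | 21 | 1.33 | 62.1% | 77.4% |

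Smaller simulations of the same kind gave 1.45 at 10%, 1.40 at 20% and 1.30 at 30%, which is agreement within simulation noise. At every p, leaving the affected patients out loses less power than keeping them.

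**The case against.** **The share is probably small.** This largely stands. Employees were registered on their first sick day, were invited to a case manager within a week, and had an OP consultation planned within two weeks. The Background says the customary advice was to rest until complaints had gone, which makes early partial return less likely. People already on sick leave before the study were handled separately. Still, the two weeks are a plan and not a criterion, and the timing indicator in Table 5 foresees first consultations that come too late.

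**Nobody is shown to have been partly at work at T0.** This stands. A reader might infer that some participants had in fact had the event. The article shows only that they were eligible. A reader might also combine "Sick leave period did not start before 2002" with "The recruitment of participants for the study started in January 2002 and ended in January 2005" and infer sick leave of up to three years at entry. The criteria permit that, but given the recruitment path it is a limit case.

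**Table 5 foresees it.** The return-to-work advice indicator has a not-applicable code for "Patient already (partially) returned to work". This is weak evidence, because the indicator is scored at every consultation, including those after allocation.

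**T0 status is recorded and an analysis plan may settle the rest.** Table 1 does schedule first RTW from the company database at T0, so the information exists. The point here concerns what the article itself fixes: an event and an entry criterion that do not fit together.

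**The main result is safe.** This stands. The article calls full RTW the primary outcome measure. Neither it nor net RTW or total days is touched.

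**Conclusion.** The point holds as a mismatch between outcome and entry criterion: first RTW can occur before randomisation, and nothing stated in the article takes such events out. The direction is towards no difference. The size depends on p, which is unknown. If inclusion kept to the planned two weeks, 5 to 10% seems a more plausible range than 20 to 30%, and an assumed hazard ratio of 1.5 would then move only to about 1.44 to 1.47. At 20 to 30% it would be about 1.3 to 1.4. The figures assume that the affected share and its pre-T0 times are alike in both arms, as randomisation implies on average.

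One stronger reading, that pre-T0 events produce negative times, does not arise on the only clock the article states, which starts on the first sick day. It would arise only if time were counted from T0 without restricting the patients.

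**What to change.** 1. In both arms, analyse first RTW only among patients with no work resumed at T0 according to the company database. This status is fixed before allocation, so the comparison stays randomised.
2. Place these patients at risk from T0: count time from T0, or, if the clock starts on the first sick day, use delayed entry at T0. State which.
3. Keep all patients in the analyses of full RTW, net RTW and total sick-leave days.
4. Report per arm the number already partly at work at T0.

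The cost is one definition, one filter on data that Table 1 already schedules, and one line in the baseline table. Slightly fewer patients enter the first-RTW analysis. For example, at an assumed 10% affected, 107 × 0.90 = 96.3 of the planned 107 per group remain. Those left out carry no information on the effect of treatment on this event.
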